## Abstract

**Background:**

Laparoscopic appendectomy has progressively gained acceptance as the standard of care for acute appendicitis. Focusing on the incidence of postoperative intra-abdominal abscess after a laparoscopic appendectomy, discordant data have been reported ranging from 1.5 to 20%. Besides, evidence advocating advantages from peritoneal irrigation over suction only are lacking. Most studies are burdened by a high level of heterogeneity regarding the severity of the appendicitis and modalities of peritoneal irrigation. One of the main drawbacks is the lack of an accepted classification for different degrees of appendicitis and peritoneal contamination. The aim of the study is to introduce a classification to clarify the relationship between grade of appendicitis, contamination, and postoperative incidence of IAA considering the surgeon’s attitude toward irrigation or suction alone. Preoperative, intra-operative, and postoperative predictive factors for infectious complication will also be assessed. This study is meant to be the first Italian multicenter resident-based observational study.

**Methods:**

Patients suffering from acute appendicitis will be enrolled during a 1-year period, according to inclusion and exclusion criteria. Participants will fill an online form reporting all clinical and intra-operative data of each patient undergoing a laparoscopic appendectomy. General surgery residents will be responsible for data collection. Our proposal of classification is based on the histological grade of appendicitis and intra-operative degree of peritoneal contamination. For each grade, a progressively increasing score is assigned.

**Discussion:**

The observational nature of this study is mandatory to examine surgeons’ attitude toward peritoneal contamination during laparoscopic appendectomy for appendicitis. Identification of different severity grades of acute appendicitis and their relationship with the development of postoperative abscesses is necessary. The resulting classification and score, even considering peritoneal lavage or suction alone, will define risk classes of peri-appendiceal contamination each one related to a specific incidence rate of postoperative IAA. Nowadays, maximum effort should be made to reach the best procedural standardization and surgical decision-making should be supported by solid evidence, especially in an emergency surgery setting.

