O/S SSI must meet the following criteria:Date of event within 30 days after surgical procedurePlus involvement of any part of the body deeper than the fascial/muscle layers that are opened or manipulated during the operative procedurePlus at least one of the following:Purulent drainage from a drain that is placed into the organ/space (for example, closed suction drainage system, open drain, T-tube drain, CT-guided drainage)Organism(s) identified from fluid or tissue in the organ/space by a culture- or non-culture-based microbiologic testing method which is performed for purposes of clinical diagnosis or treatmentAn abscess or other evidence of infection involving the organ/space that is detected on the gross anatomical or histopathologic exam, or imaging test evidence suggestive of infectionPlus at least one criterion for a specific organ/space infection site listed in the CDC/NHSN Surveillance Definitions for Specific Types of Infections [7] part of 2019 Patient Safety Component Manual from Center for Disease Control and Prevention and National Healthcare Safety Network (NHSN) [8]

The average reported incidence of IAA following a laparoscopic appendectomy in the literature ranges from 1.5 to 20% with extreme heterogeneity in the types of studies considered [4, 5, 9–11].

Few studies analyzed risk factors for the development of IAA after LA. Body mass index, leukocytosis, perforated appendicitis, and operative time > 90 min were associated with the development of postoperative IAA using multivariate analysis [12–14]. A retrospective single-center analysis performed by Cho et al. with 1822 patients identified intra-abdominal irrigation as the only risk factor associated with IAA [9].

Evidence regarding advantages from peritoneal irrigation over suction only are scarce. Both guidelines from the World Society of Emergency Surgery (WSES) and from European Association for Endoscopic Surgery do not report any advantages from this practice, supported by low levels of evidence (LOE 2, GOR B) [1, 2].

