## Hypothesis, design of the study, and aims

The driving hypothesis of our study is that there should exist a relationship between different intra-operative treatment protocols (irrigation vs suction alone) and postoperative incidence of IAA. Furthermore, considering various grades of appendicitis and peritoneal contamination, the use of irrigation vs suction alone could lead to different rates of postoperative IAA.

The aim of this study is to introduce and evaluate a classification for acute appendicitis taking into account the peritoneal contamination to delineate the relationship between grade of appendicitis and postoperative incidence of IAA considering the surgeon’s attitude toward irrigation or suction alone. Some studies described that the incidence of postoperative IAA is higher in the perforated appendix [12, 13]. No clear evidence exists exploring the severity of peritonitis as a potential predictor of IAA and its relationship with irrigation or suction alone.

This is a prospective observational multicenter study.

Primary endpoint:Relationship among each severity grade of acute appendicitis and postoperative incidence of intra-abdominal abscesses

Secondary endpoint:Impact of intraperitoneal irrigation or suction alone on the incidence of IAA for each severity grade

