### Data collection and statistical analysis

Participants will fill an online form reporting all clinical and intra-operative data of each patient who will undergo a laparoscopic appendectomy. All personal information of patients will be removed according to data anonymization.

Data will be reported in accordance with Strengthening the Reporting of Observational studies in Epidemiology guidelines (STROBE) for observational studies [22].

Residents from each involved center will be responsible for data collection.

All forms will be collected in an electronic database by the coordinating residents who will check for data completeness. All residents taking part in the study will be asked to enter eventual missing data.

The incidence of IAA after laparoscopic appendectomy reported in the literature ranges from 1.5 to 20% [4, 5, 9–11]. Such a wide interval is not negligible when calculating the sample size (*n*) of the study cohort. Furthermore, some important basic considerations need to be taken into account: appendicitis is the most common acute surgical disease so the baseline population is large and cannot be exactly estimated; the incidence of intra-abdominal abscesses has never been systematically investigated in regard to the severity of appendicitis and contamination. All patients included in the study will be classified into different clusters considering the grade of appendicitis and contamination, lavage vs suction alone, and postoperative incidence of IAA.

Considering all these aspects, sample size for power calculation can be reasonably estimated given a 95% confidence interval with a *z*-score of 1.96, a 50% standard deviation, and a 0.03 margin of error. This formula does not include the incidence rate of IAA for the aforementioned reasons.

The estimated sample size would be around at least 1067 patients. Data will be collected in a computerized spreadsheet (Microsoft Excel 2016; Microsoft Corporation, Redmond; WA) and analyzed with statistical software (IBM Corp. Released 2017. IBM SPSS Statistics for Windows, version 25.0. Armonk, NY).

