*χ*^*2*^ test will be assessed to compare categorical variables, and univariate logistic regression will be performed to provide hazard ratios for individual variables, identifying possible predictors of postoperative complication (IAA above all). All significant (*p* < 0.05) variables at univariate analysis will be included in a multivariate regression model in order to detect independent risk factors for the outcome and to estimate odds ratio and 95% confidence intervals.

A scoring system will be built according to the results of statistical analysis. The weight of each variable will be addressed based on odds ratio values. To evaluate the accuracy of the score, discrimination and calibration of the model will be explored. The former will be assessed by receiver operating characteristic (ROC) curve analysis, whereas the latter will be investigated with the Hosmer-Lemeshow goodness-of-fit test. Based on the results of the ROC curve analysis, we will proceed to identify different severity grades of acute appendicitis each one related to a specific risk of developing delayed IAA. *χ*^*2*^ test will be assessed to compare categorical variables, and univariate logistic regression will be performed to provide hazard ratios for individual variables, identifying possible predictors of postoperative complication (IAA above all). All significant (*p* < 0.05) variables at univariate analysis will be included in a multivariate regression model in order to detect independent risk factors for the outcome and to estimate odds ratio and 95% confidence intervals.

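### The protocol defines severity grade in two ways; one lets irrigation into the grade within which irrigation is to be judged, and the secondary endpoint does not say which applies

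*Protocol article*

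**What the plan says.** The protocol article gives two accounts of how a patient is graded.

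- **Disease-only.** Abstract, Methods: "Our proposal of classification is based on the histological grade of appendicitis and intra-operative degree of peritoneal contamination". The Classification section and Table 1 agree: one appendix aspect and one contamination type per patient, with no treatment variable.
- **Score-derived.** Data collection and statistical analysis sets an entry threshold of p < 0.05, and the rule reads: "variables at univariate analysis will be included in a multivariate regression model in order to detect independent risk factors for the outcome". A score follows: "The weight of each variable will be addressed based on odds ratio values". From the ROC analysis of that score, "we will proceed to identify different severity grades of acute appendicitis each one related to a specific risk of developing delayed IAA". Lavage with suction versus suction alone, and lavage volume, are listed among the operative data in Methods. Nothing removes them from the candidate variables.

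The Discussion of the abstract says of the result: "The resulting classification and score, even considering peritoneal lavage or suction alone, will define risk classes of peri-appendiceal contamination".

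The secondary endpoint, in Hypothesis, design of the study, and aims, is: "Impact of intraperitoneal irrigation or suction alone on the incidence of IAA for each severity grade". It does not say whether the grade is the Table 1 classification or the class cut from the score.

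**The concern.** The secondary endpoint uses the term that the statistical section gives to the score-derived classes. On that reading, and if irrigation earns points, the exposure becomes part of the stratum in which it is tested. Two patients with the same appendix and the same contamination can then fall in different grades because one was irrigated. Within a grade, irrigated and suction-only patients differ systematically in disease.

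Entry of irrigation is not remote. A link between irrigation and abscess is the study's driving hypothesis, and the introduction cites a 1822-patient retrospective series that "identified intra-abdominal irrigation as the only risk factor associated with IAA".

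At stake is the per-grade irrigation result, which the Conclusions present as the main practical use of the score. A grade that moves with the surgeon's choice cannot guide that choice.

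**Working it through.** **The plan's own figure.** The inputs are z = 1.96, "a 50% standard deviation, and a 0.03 margin of error". Then n = z² × p(1 − p) / d² = 1.96² × 0.5 × 0.5 / 0.03² = 0.9604 / 0.0009 = 1067.1, which agrees with the stated 1067. It is used below only as the study size.

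**Algebra.** Write T = 1 for irrigation and 0 for suction alone, S for the disease part of the log-odds and b for the log-OR of irrigation:

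logit P(IAA) = a + S + bT

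If grades are cut on S + bT, patients with equal scores have equal risk whatever T is, so the irrigation OR at a fixed score is 1 for any b. Example with assumed ORs of 2 for a gangrenous appendix (against an erythematous one) and 2 for irrigation:

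- gangrenous, suction alone: ln 2 + 0 = 0.69
- erythematous, irrigated: 0 + ln 2 = 0.69

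The two patients have the same score and risk but different disease. Grades are coarser than exact scores, so part of the effect can survive, and single grades can go either way.

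**Size, simulation A.** The documents give no irrigation effect, share irrigated, severity distribution or cut-points, so these are assumptions: appendix-aspect ORs 1/1.4/2/3; contamination ORs 1/1.7/2.5/4; 43% to 51% irrigated; abscess incidence 3% to 9%, inside the protocol's 1.5% to 20%; 3, 4 or 6 quantile classes in place of the unstated ROC cuts; points from log-ORs or raw ORs; with and without confounding by indication; 2,000,000 patients per scenario. The figures are Mantel-Haenszel ORs pooled over grades.

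| True irrigation OR | Grades from disease only | Grades from disease + irrigation |
|---|---|---|
| 0.5 | 0.50 to 0.54 | 0.79 to 1.00 |
| 1.5 | 1.51 to 1.63 | 0.89 to 1.20 |
| 2.0 | 1.99 to 2.17 | 0.98 to 1.48 |
| 3.0 | 2.97 to 3.20 | 0.95 to 1.68 |

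The small excess in the middle column is residual confounding within coarse grades. With irrigation in the score, the lowest grade always held one treatment group only, and a single grade could reverse (0.73 at a true OR of 1.5).

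**Size, simulation B.** Five contamination levels with log-odds from 0 to 2.2, irrigation rising from 20% to 80% with level, reference risk about 1.8%. A true OR of 2.0 was recovered within disease levels but came out at about 0.8 to 1.5 within irrigation-containing classes, depending on the cuts and the level frequencies. A true OR of 1.5 gave 1.10 to 1.68, so a weak effect need not be attenuated.

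**Would irrigation enter?** The rule is univariate p < 0.05, so the crude association decides. With n = 1067 and the inputs of simulation B:

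- True OR 0.5: irrigating the sicker patients brings the crude OR to about 0.92 to 0.98, and irrigation enters in about 5% of studies.
- True OR 1.5 or more: it enters in about 97% of studies or more.

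Simulation A with milder confounding shows the same pull: crude ORs of 0.72, 2.11, 2.79 and 4.06 for true ORs of 0.5, 1.5, 2.0 and 3.0. The 0.5 row of the table therefore applies only where irrigation does get in, which strong confounding makes rare.

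**The case against.** The best defence is that the protocol already has a disease-only classification (Abstract, Methods; Classification; Table 1), and that Methods records the grade as an intra-operative finding. If the secondary endpoint uses that grade, the problem does not arise. This stands as a possible reading, but the endpoint does not select it, and the statistical section gives the same term to the score classes.

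The abstract's phrase about considering lavage or suction is also weak evidence that lavage is a score component. Elsewhere the article uses considering for something read alongside the grade, and the sample-size paragraph lists lavage apart from grade and next to the outcome. This stands too. The point therefore rests on the variable-selection rule, which admits irrigation without that phrase.

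A reader might infer three stronger things that the documents do not support:

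- **That the secondary endpoint is biased to no effect by construction.** This needs the score-derived grades and irrigation in the score. Neither is certain, and weak effects are not reliably attenuated.
- **That a benefit or harm of irrigation would be hidden.** If irrigation enters, the same multivariable model reports its adjusted OR with a 95% confidence interval. Only the per-grade reading is distorted.
- **That drain, operator and operative time must also be barred.** They are management rather than disease, but no calculation shows that their presence distorts the irrigation comparison.

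**Conclusion.** The concern holds as an unresolved choice between two definitions of severity grade, one of which can undermine the secondary endpoint. If the score-derived grades are used and irrigation has entered, the per-grade irrigation comparison is distorted: generally toward no effect for moderate or strong effects, unpredictably for weak ones, and with no comparison possible in any grade that holds one treatment group. Entry is likely when irrigation is associated with more abscesses, truly or through confounding by indication, and unlikely when a protective effect is masked by that confounding.

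The direction at a fixed score follows from the algebra. All sizes rest on the assumed effect sizes, irrigation shares, severity mix and cut-points, and are illustrative.

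**What to change.** Add two sentences to Data collection and statistical analysis, and refer to them from the endpoints:

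1. The severity grades used for the primary and secondary endpoints are built only from the Table 1 disease findings (appendix aspect and contamination type); irrigation and lavage volume do not contribute to the score that defines them.
2. Irrigation is analysed as the exposure, within those grades or as a grade-by-irrigation interaction, adjusted for confounders.

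Any prediction model that includes treatment can be reported separately and should not be called a severity grade. The abstract's sentence on the score should be reworded to match.

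Cost: no extra data or patients. The severity score may show a slightly lower AUC than one that includes irrigation.

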## Introduction, background, and rationale

Acute appendicitis (AA) is one of the leading causes of acute abdominal pain, and its highest incidence is among children, adolescents, and young adults. The lifetime risk is 8.6% and 6.7% respectively for males and females. Considering the progression of the disease, the therapeutic mainstay is surgical removal of the appendix [1, 2].

Laparoscopic appendectomy has gained acceptance as the standard of care for acute appendicitis after several randomized controlled trials (RCTs) and case-control studies demonstrated clear advantages. Compared to an open appendectomy (OA), a laparoscopic appendectomy (LA) has better outcomes in terms of surgical site infections, time to oral intake, and length of stay (LOS). On the other hand, longer operative times are associated with LA. Considering the incidence of postoperative intra-abdominal abscess (IAA), controversies have been reported during the last few years. A trend toward a higher incidence of IAAs was reported in a systematic review in 2010 [3], though no consistent results were seen from more recent papers [2, 4, 5].

IAA is considered an intra-abdominal organ/space surgical site infection as defined in the Center for Disease Control Surgical Site Infection Criteria, introduced in 1992 [6].

Briefly, surgical site infections (SSIs) are divided into three categories: superficial incisional SSI (SI SSI), deep incisional SSI (DI SSI), and organ/space surgical site infection (O/S SSI). Each category has defined inclusion criteria.

O/S SSI must meet the following criteria:Date of event within 30 days after surgical procedurePlus involvement of any part of the body deeper than the fascial/muscle layers that are opened or manipulated during the operative procedurePlus at least one of the following:Purulent drainage from a drain that is placed into the organ/space (for example, closed suction drainage system, open drain, T-tube drain, CT-guided drainage)Organism(s) identified from fluid or tissue in the organ/space by a culture- or non-culture-based microbiologic testing method which is performed for purposes of clinical diagnosis or treatmentAn abscess or other evidence of infection involving the organ/space that is detected on the gross anatomical or histopathologic exam, or imaging test evidence suggestive of infectionPlus at least one criterion for a specific organ/space infection site listed in the CDC/NHSN Surveillance Definitions for Specific Types of Infections [7] part of 2019 Patient Safety Component Manual from Center for Disease Control and Prevention and National Healthcare Safety Network (NHSN) [8]

The average reported incidence of IAA following a laparoscopic appendectomy in the literature ranges from 1.5 to 20% with extreme heterogeneity in the types of studies considered [4, 5, 9–11].

Few studies analyzed risk factors for the development of IAA after LA. Body mass index, leukocytosis, perforated appendicitis, and operative time > 90 min were associated with the development of postoperative IAA using multivariate analysis [12–14]. A retrospective single-center analysis performed by Cho et al. with 1822 patients identified intra-abdominal irrigation as the only risk factor associated with IAA [9].

Evidence regarding advantages from peritoneal irrigation over suction only are scarce. Both guidelines from the World Society of Emergency Surgery (WSES) and from European Association for Endoscopic Surgery do not report any advantages from this practice, supported by low levels of evidence (LOE 2, GOR B) [1, 2].

Furthermore, three randomized control trials and two retrospective observational studies have been analyzed in a recent systematic review and meta-analysis. These studies are burdened by a high level of heterogeneity regarding the severity of appendicitis and modalities of peritoneal irrigation [15]. No advantages from peritoneal irrigation have been identified to date. This data are confirmed by a more recent meta-analysis in which heterogeneity of patients has been highlighted [16].

With the current literature, one of the main bias affecting all studies is the lack of a universally accepted classification method for different degrees of appendicitis and peritoneal contamination. Therefore, to establish the effective relationship between contamination, degree of intra-operative irrigation, and postoperative IAA incidence, it is mandatory to apply a specific classification, based on the intra-operative scenario. The grading system already published by WSES for acute appendicitis is a useful tool for a comprehensive evaluation of patients [17]. A system based on an exclusive and accurate focus on peritoneal contamination plus the histological grade of inflammation is nevertheless lacking.

This study is meant to be the first Italian multicenter resident-based study. This is due to the scarce involvement of General Surgery Italian residents in scientific projects. Residents have the responsibility to take care of patient selection, personal involvement in surgery, intra-operative data collection, postoperative follow-up, and related data collection, data analysis, and study writing.

## Hypothesis, design of the study, and aims

The driving hypothesis of our study is that there should exist a relationship between different intra-operative treatment protocols (irrigation vs suction alone) and postoperative incidence of IAA. Furthermore, considering various grades of appendicitis and peritoneal contamination, the use of irrigation vs suction alone could lead to different rates of postoperative IAA.

The aim of this study is to introduce and evaluate a classification for acute appendicitis taking into account the peritoneal contamination to delineate the relationship between grade of appendicitis and postoperative incidence of IAA considering the surgeon’s attitude toward irrigation or suction alone. Some studies described that the incidence of postoperative IAA is higher in the perforated appendix [12, 13]. No clear evidence exists exploring the severity of peritonitis as a potential predictor of IAA and its relationship with irrigation or suction alone.

This is a prospective observational multicenter study.

Primary endpoint:Relationship among each severity grade of acute appendicitis and postoperative incidence of intra-abdominal abscesses

Secondary endpoint:Impact of intraperitoneal irrigation or suction alone on the incidence of IAA for each severity grade

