## Discussion

The observational nature of this study is mandatory to examine and analyze surgeon attitude toward peritoneal contamination related to appendicitis during laparoscopic appendectomy. The optimal study design to address the core matter would be a well-structured RCT to assess the real effect of lavage plus suction versus suction alone on postoperative IAA. As above reported in the “Introduction, background, and rationale” section, there is a lack of methodological strictness in the existent randomized trials due to heterogeneous determination of appendicitis severity and peritoneal contamination.

We feel indispensable to start from identifying different grades of appendicitis, related contamination, and their relationship with postoperative abscesses, considering surgeons’ attitude. The core step is to classify each patient and create a score to pick out classes of peri-appendiceal contamination related to different incidence rate of postoperative IAA.

The General Surgery residency program at the University of Milan is based on a large clinical network in which residents are distributed in different hospitals. It is a 5-year program. One hundred thirty residents are involved. The clinical network includes 59 surgical units in 27 hospitals.

This system structure allows great exposure to different surgical scenarios, inside and outside the operating room. The program requires, per year, a minimum of procedures in which the resident has to be involved. From the first to the fifth year, the difficulty of the procedure is increased. To the best of our knowledge, this is one of the most efficient residency programs in Italy because great attention is dedicated to surgical skills improvement. On the other hand, this program may underestimate the scientific needs and educational growth of residents. This study is resident driven as an incitement to a defined organization for the scientific growth of the University of Milan residents.

During the project start-up phase of this study, an official group of residents of the General Surgery program at the University of Milan has been created. The main aim of this group of young doctors is to try to guarantee to each resident, who is interested, the minimal scientific knowledge and ability to critically understand, ideate, and project a scientific study.

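### The per-grade irrigation endpoint has no fitting adjusted analysis: irrigation and its confounders enter only if univariately significant, and the model gives one overall odds ratio

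*Protocol article*

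**What the plan says.** The section on hypothesis, design and aims sets the secondary endpoint as "Impact of intraperitoneal irrigation or suction alone on the incidence of IAA for each severity grade". The hypothesis behind it is that, "considering various grades of appendicitis and peritoneal contamination, the use of irrigation vs suction alone could lead to different rates of postoperative IAA". This is a statement about effect modification by grade. Irrigation is not allocated: "This is a prospective observational multicenter study", and the aim is pursued "considering the surgeon’s attitude toward irrigation or suction alone".

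The section on data collection and statistical analysis lists the methods. A chi-square "test will be assessed to compare categorical variables, and univariate logistic regression will be performed". Every variable with univariate p < 0.05 then goes into a multivariate regression model meant to find independent risk factors, reported as odds ratios with 95% confidence intervals. A score is built from those odds ratios, and the severity grades follow from a ROC analysis of the score. The text does not say which of these methods serves the secondary endpoint.

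**The concern.** Two features of the stated analysis do not fit the endpoint.

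- **The entry rule.** When surgeons choose irrigation, its unadjusted association with abscess reflects both any effect and the kind of case that gets irrigated. If irrigation tends to go to the worse cases, a protective effect and the indication pull in opposite directions. The crude result can then be near null, and irrigation is left out of the only adjusted model. The rule can also drop a confounder that narrowly misses p < 0.05.
- **The estimand.** A model of independent risk factors, as described, gives a single irrigation odds ratio if irrigation enters at all. The endpoint asks for one per grade, and the hypothesis asks whether they differ. The only listed tool that naturally gives a within-grade comparison is the chi-square test. It is unadjusted, and a set of separate tests does not test a difference between grades.

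The Conclusions section names, as the largest practical consequence of the score, the identification of intra-operative situations in which the role of irrigation is clear. The stated analysis may give no adjusted irrigation estimate at all, and none by grade.

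**Working it through.** **The plan's own figure.** The sample size uses z = 1.96, p = 0.5 and a margin of 0.03: n = 1.96² × 0.25 / 0.03² = 1067.1, so the stated 1067 reproduces. It is a precision calculation for one proportion. It contains no irrigation effect and no grade.

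**Effect of the entry rule.** From the protocol: n = 1067 and entry at p < 0.05 (taken as two-sided). The grade mix, irrigation shares and abscess risks are assumptions, because the protocol gives only an overall literature range of 1.5% to 20%. Three grades are used for illustration.

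*Strong gradient:* grade mix 60/30/10%, irrigation 20/60/90%, risk without irrigation 2/5/20%, true irrigation odds ratio 0.5 in every grade.

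- Risk with irrigation, from halved odds: 1.01%, 2.56%, 11.11%.
- Share irrigated: 0.12 + 0.18 + 0.09 = 0.39, so 416 irrigated and 651 not.
- Irrigated: (0.12 × 0.0101 + 0.18 × 0.0256 + 0.09 × 0.1111) / 0.39 = 4.06%.
- Suction alone: (0.48 × 0.02 + 0.12 × 0.05 + 0.01 × 0.20) / 0.61 = 2.89%.
- Crude OR = (0.0406/0.9594) / (0.0289/0.9711) = 1.42, the wrong direction.
- Expected counts are 16.9 and 399.2 (irrigated) and 18.8 and 632.1 (suction). SE of the log OR = √(1/16.9 + 1/399.2 + 1/18.8 + 1/632.1) = 0.341, and z = ln 1.42 / 0.341 = 1.03.
- Chance of passing the screen = Φ(1.03 − 1.96) + Φ(−1.03 − 1.96) ≈ 18% (17% to 19% depending on the variance used).

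The same steps for the other cases:

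| Assumed gradient | True OR in each grade | Irrigated | Suction | Crude OR | Passes screen |
|---|---|---|---|---|---|
| Strong | 0.5 | 4.06% | 2.89% | 1.42 | about 18% |
| Strong | 1.0 | 7.54% | 2.89% | 2.74 | about 92% |
| Mild | 0.5 | 2.47% | 3.76% | 0.65 | about 22% |
| Mild | 1.0 | 4.73% | 3.76% | 1.27 | about 12% |

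(Mild: same grade mix, irrigation 40/50/60%, risk 2/5/15%.)

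Under the strong gradient the rule usually admits irrigation when it does nothing and usually leaves it out when it helps. Under the mild gradient it also usually leaves out a halving of the odds. There the small number of events (about 34) contributes as well as the confounding.

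**What the data can carry.** Expected events are 1067 × 0.015 = 16 at the low end of the literature range, 53 at an assumed 5%, and 1067 × 0.20 = 213 at the top. With four equal grades and a 1:1 irrigation split (both assumed) there are 1067 / 8 = 133 patients per arm per grade. Power to detect a halving of abscess incidence within a grade is then 8% at 1.5% incidence, 19% at 5%, 34% at 10% and 63% at 20%.

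**The case against.** The strongest reply is that a multivariate model is planned and that severity, contamination, ASA, Charlson, PIRO, CRP and operator are all collected, so adjustment is available. This stands. A reader might infer that irrigation will be judged only by unadjusted tests. The documents do not support that: they plan an adjusted model and do not assign any test to this endpoint. That chi-square would be used within grades is an inference. Adjustment nevertheless depends on the p < 0.05 screen.

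It can also be said that interaction terms and clustering belong in a fuller protocol or SAP that is not shown. This stands for silence alone. It does not cover the entry rule, which is written down and would apply as worded.

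Three stronger readings should be set aside.

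- *Irrigation with no effect will look harmful.* It may. The protocol does not say that dirtier cases are irrigated more. The mild gradient gives only 1.27, and these crude figures pool the grades; confounding left within a grade would be smaller.
- *Clustering badly inflates type I error.* With 27 hospitals and whole-sample clusters of 1067/27 = 39.5 patients, an assumed ICC of 0.01 to 0.05 gives design effects 1 + (m − 1) × ICC of 1.39 to 2.93, and error of 10% to 25% if irrigation is wholly a centre habit. Within one of four equal grades, m is about 9.9, the design effect 1.09 to 1.44 and the error about 6% to 10%. With 59 units it is about 5% to 7%. Moreover, "The clinical network includes 59 surgical units in 27 hospitals" describes the residency network, not the participating centres.
- *Testing the 4 + 6 categories of Table 1 separately gives a 40% chance of a false positive (1 − 0.95¹⁰).* Those tests share the same patients and are not independent, and the categories are not the planned grades, which come from the ROC step.

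The Discussion section also concedes that a randomised trial would be the optimal design for the lavage question. That supports wording results as associations but does not repair the model rule.

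**Conclusion.** The concern holds in a limited form. For the secondary endpoint, the only adjusted analysis stated admits irrigation and each confounder on univariate significance. As described, it yields at most one overall irrigation odds ratio, although the endpoint is per grade. The rule can conceal a real effect: in the illustrations a true odds ratio of 0.5 reaches the adjusted model only about 18% to 22% of the time. Those figures rest on assumed grade mixes, irrigation shares and risks, so they show the mechanism and a plausible size, not a prediction.

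The plan is not confined to unadjusted tests, and the documents do not establish a particular multiplicity or clustering error rate. Clustering by centre is a supporting refinement. The change should be made before the analysis. It does not affect data collection on patients or the primary endpoint.

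**What to change.** For the secondary endpoint only, replace univariate screening with one prespecified logistic model:

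- **Terms forced in whatever their univariate p:** irrigation, severity grade and the irrigation-by-grade interaction. Treat grade as categories unless an order is fixed in advance, since a single trend term would constrain the per-grade odds ratios.
- **Confounders:** a short list, already collected, that precedes the irrigation decision, for example age, ASA or Charlson, PIRO or CRP, and operator. Do not enter contamination again if the grade already includes it. Do not adjust for variables that may follow from irrigation, such as operative time, drainage or antibiotic duration.
- **Few events:** with four grades the forced terms take 1 + 3 + 3 = 7 parameters, and four one-parameter covariates make 11. That is about 1.5 events per parameter at 16 events and 4.8 at 53. State that the covariate list will be shortened or Firth penalised estimation used if events are few.
- **Centre:** a random intercept or centre-robust standard errors.
- **Report:** per-grade odds ratios with 95% CIs and the interaction test, worded as association.

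The risk-factor model can remain for the score. The cost is analysis wording, slightly more work and wider confidence intervals. No new clinical variable is needed. The article's data list does not name a centre identifier, so confirm that each form carries one; residents collect the data centre by centre.
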